### Recruitment

Recruitment is anticipated to occur mainly through targeted online advertising. Other recruitment techniques will include the use of flyers, which will be displayed in the waiting rooms of health services and other conspicuous locations. Print and radio advertisements will be included where possible. Following initial contact by potential participants, a researcher will establish that inclusion and non-inclusion criteria are satisfied. Written informed consent for the trial will be obtained from all participants at the first meeting.

### Trial procedure

All participants will provide informed written consent before they undergo a baseline face-to-face interview with a trained researcher. Participant contact will be conducted using procedures adapted from the treatment manual for the Healthy Lifestyles Program [18, 19]. Consented participants are randomised to receive NAC or placebo through a 1:1 allocation ratio and commenced on a standardised smoking cessation program using the automated QuitCoach website. The QuitCoach is a tailored, Internet-delivered smoking cessation advice program [20]. It is designed to replicate face-to-face multi-session smoking cessation counselling. QuitCoach has been shown to be well accepted by people who are planning to quit smoking and can be successfully combined with pharmacotherapy [21]. Participants will be randomly and sequentially allocated, in a double-blind fashion, to receive NAC or placebo from day 0 of the treatment phase of the study to the end of week 16. A fixed dose regime of 1.8 g/day of NAC, administered as one 900 mg effervescent tablet, is to be dissolved in a glass of water and consumed, twice daily. To facilitate the double-blinding process, the trial medications (both NAC and placebo) will be dispensed in identical numbers and tablet formulations in sealed containers by the trial pharmacist, who will also perform the tablet counts to monitor adherence. Participants will collect their medications from the trial clinician at baseline and at the eight-week study visit.

### Collection and handling of biological samples

Saliva will be collected at baseline and at weeks 8, 16 and 42 for COT measurements. Before the baseline meeting, participants will be provided with the following instructions: (1) avoid foods with high sugar or acidity, or high caffeine content immediately before sample collection; (2) do not eat a major meal within 60 min of sample collection; (3) do not consume alcohol within 12 h of sample collection; (4) participants should not brush their teeth within 45 min before sample collection; (5) dental work should not be performed within 24 h before sample collection. The trial clinician will document consumption of alcohol, nicotine, caffeine and medications in the 12 h before collection, as well as vigorous physical activity and the presence of oral disease or injury. Saliva collection is performed by instructing participants to allow saliva to pool in the mouth and then drool through the Salimetrics Saliva Collection Aid into a cryovial. This sample is stored in a – 80 °C freezer until it is time for analysis. An enzyme-linked immunosorbent assay (ELISA) will be performed to determine levels of COT in the samples. Samples are collected at each participant meeting.

### Allocation and concealment

Individuals will be assigned in a 1:1 ratio using permutated block randomisation to treatment with NAC or placebo, in a double-blind fashion. The randomisation code is generated by an independent researcher and held by the pharmacy to maintain blinding. The randomisation code remains concealed until all data analysis has been completed (triple-blind design). Unblinding for emergency situations is undertaken by the pharmacy, with the approval of the Principle Investigator.

### Treatment adherence and fidelity

The trial medications will be supplied by the trial pharmacist; participants will be instructed to return all containers to allow capsule counts. Concordant with SPIRIT guidelines, adherence will be assessed by pill counts of returned medication packs. Use of QuitCoach will be monitored by participant self-report (Additional file 1).

## Variables and instruments

The primary outcome of this aid-to-cessation trial will be between-group differences in continuous abstinence for the 26-week period between weeks 16 and 42. The primary outcome is measured at six months post-treatment discontinuation (week 42) rather than at treatment discontinuation (week 16), in line with the Russell Standard for international smoking cessation research [22]. To assess self-reported smoking habits, participants will complete a timeline followback (TLFB) at each contact visit. This measure has been shown to be accurate up to 12 months before interview [23]. Abstinence from smoking will be measured by self-report, exhaled carbon monoxide (CO_EXH_) < 10 ppm measured using a Micro+ Smokerlyzer (Bedfont Scientific) and salivary COT < 50 ng/L, which is a sufficient margin to allow for passive tobacco smoking. CO_EXH_ may be < 10 ppm in non-abstinent participants who have not smoked within 2 h [24]. Smoking cessation will be confirmed if CO_EXH_ levels are < 10 ppm and COT is < 50 ng/mL. Where participants self-report use of non-tobacco nicotine, CO_EXH_ will be used to confirm abstinence. Secondary outcomes will include the timing of the first lapse and first relapse, based on a dichotomous variable and defined as self-reported smoking seven days in a row at any time between two weeks after quitting and the trial end. Prolonged abstinence will also be reported and defined as any slips or lapses following the quit date [25].

At the baseline visit, the Fagerström Test for Nicotine Dependence and a smoking history questionnaire will be administered. The smoking history questionnaire will explore how long the participant has smoked for (e.g. age of first use, duration of use), their average consumption of cigarettes and the number of previous attempts to quit smoking. Data will also be collected regarding how determined they are to give up smoking on this attempt (on a Likert scale of 1–4) and to rate their chances of permanently quitting on this attempt (on a Likert scale of 1–6). The Minnesota Nicotine Withdrawal Scale will be administered to assess urge to smoke among other withdrawal symptoms, depressed mood, irritability, anxiety, difficulty concentrating, restlessness, increased appetite and sleep. Participants will also complete the Brief Questionnaire of Smoking Urges, which assesses cravings related to desire to smoke and expectations of positive effects anticipation of relief from negative affect. Demographic data, lifetime history of smoking (e.g. motivation, readiness to quit, previous attempts), level of social support, self-reported medical and psychiatric history will also be collected at baseline. A psychiatric diagnostic interview (SCID-5-RV), based on the DSM-5 will be conducted at baseline. The WHO ASSIST and AUDIT will be collected at baseline and visits at weeks 8 and 42. The Standardised Assessment of Personality – Abbreviated Scale (SAPAS), a brief screen for personality disorder, will be used at baseline. The WHO-5, Depression, Anxiety, and Stress Scale (DASS-21) and K10 will be administered at baseline and at weeks 8, 16 and 42 (Table 1). To optimise retention and adherence with the treatment protocols, telephone contact will be made with each participant once a fortnight beginning one week after baseline. Progress and adherence self-report data will be recorded on a questionnaire at these telephone calls. Participant reports of adverse effects will be recorded, appropriate interventions according to medical assessment will be implemented and AEs will be further monitored. Six months following the final study visit the participant will be contacted and a follow-up questionnaire conducted to assess if participants have continued to smoke, and at what level, since completing the trial. CO_EXH_ and COT measures will be taken.

**Table 1 Tab1:** Summary of measures collected and other activities at each study visit

	Baseline	8 weeks	16 weeks	42 weeks (follow-up)
Demographic/health questionnaire	X			
Fagerström Test for Nicotine Dependence	X	X	X	X
Lifetime history of smoking	X			
SCID −5-RV	X			
SAPAS	X			
Exhaled CO (CO_EXH_)	X	X	X	X
MNWS	X	X	X	X
QSU-brief	X	X	X	X
Salivary cotinine	X	X	X	X
K10, DASS-21	X	X	X	X
AUDIT	X		X	X
WHO-5	X	X	X	X
WHO ASSIST	X		X	X
TLFB	X	X	X	
Dispensing of study medications	X	X		

Safety and tolerability outcomes will be assessed by comparison of reported AEs for all NAC-treated and placebo-treated participants and for subgroups. Subgroup analyses will be performed for groups categorised by variables including gender and SCID diagnosis. Participants will be considered to have completed the study if they completed all follow-up examinations to week 42. Individuals who never quit or who relapse (defined as smoking on seven consecutive days), will be examined separately as well as pooled as treatment failures. Non-cigarette tobacco use, but not non-tobacco nicotine use, will be categorised as smoking.

Intended use of bupropion, varenicline or NRT during the 42-week trial period will not be permitted but is only a withdrawal criterion if used during the 16-week treatment period. Some participants may decide to use NRT during the 42-week study. Although this is contrary to the directions given to participants in the study, it is not a study withdrawal criterion and these participants may remain in the study. COT levels will be measured using chromatographic techniques.

## Key outcome variables

### Data management and integrity

#### Confidentiality

Records of participation in this study will be held confidential so far as permitted by law. This will include de-identification of all documents relating to the trial by assigning a random number that will identify participants in terms of a dataset and not an individual. However, researchers, regulatory agencies and the Barwon Health Human Research Ethics Committee (HREC) will be able to inspect and have access to confidential data that identify participants by name.

#### Inter-rater reliability

The measures listed under ‘Variables and instruments’ in the study design section will be co-rated by trained trial clinicians. Inter-rater reliability will be checked before commencement of the trial and repeated every six months during the trial, using a standardised videotaped patient interview. Raters will need to achieve an intraclass (model 2,1) correlation score of 0.8 and will undergo further training as necessary during the study to maintain inter-rater reliability.

#### Sample size

The sample size was initially determined to be 360. In order to detect a 7% difference between the groups (with six-month smoking cessation, including participant attrition estimated at 1%), the sample size has been calculated for a Cochran-Mantel-Haenszel (CMH) test to acknowledge a cluster randomised design with three recruitment centres as strata (each with an overall six-month smoking cessation of 1% for placebo). A sample size of 180 in the NAC group and 180 in the control group (across three roughly equal size strata) achieves 80% power to detect an odds ratio (OR) = 7, assuming a two-sided type I error of 0.05. The sample size also achieves 80% power to detect a 7% difference in six-month smoking cessation between NAC and placebo groups assuming two-sided alpha = 0.05 and an 8% inflation of the required sample size due to clustering. However, the current trial has a recruitment target of 120 in total, with the intention of scaling up as more funding is acquired.

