### Study aims and hypotheses

The aim of this study is to investigate the efficacy of NAC (1.8 g/day) for smoking cessation in a randomised, placebo-controlled trial of current smokers who wish to quit smoking. The primary outcome measure will be 24 weeks of continuous abstinence from end of treatment (EoT; 16 weeks) in tobacco smoking, confirmed by biological measures. Secondary outcome measures include point prevalence abstinence, time to relapse and total cigarette consumption. Safety, tolerability and subgroup analyses will also be conducted.

It is hypothesised that: (1) treatment with NAC will be superior to placebo for smoking cessation at follow-up (week 42), confirmed by assaying exhaled carbon monoxide, salivary cotinine (COT); and (2) treatment with NAC will be superior to placebo for smoking cessation at treatment endpoint (week 16), confirmed by assaying exhaled carbon monoxide, salivary COT.

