#### Statistical analysis

A modified ‘intention-to-treat’ approach, following CONSORT Statement guidelines, will be used. Missing values will be scrutinized to check for non-random distribution and analyses that utilize baseline data will be executed twice: once using observed data and once using multiple imputation under multivariate normal assumptions. The CMH test will be used to compare the proportions of relapse between the treatment groups (control versus intervention). The common OR and its 95% confidence interval will also be reported as well as the results of the Breslow-Day test for homogeneity of the ORs across the strata. In further supportive analyses, generalized linear mixed models (GLMMs) will be used to compare the rates of relapse after adjusting for baseline measurements and to explore possible interactions between baseline factors and the intervention. Average treatment group differences for the continuous secondary outcomes will be examined using a likelihood based mixed-effects model, repeated measures approach (MMRM). The MMRM models include the fixed categorical effects of treatment, visit and treatment-by-visit interaction, as well as the continuous fixed covariates of baseline score and baseline score-by-visit interaction. Effect sizes will be calculated using Cohen’s guidelines. All comparisons will be conducted using a two-sided alpha level of 0.05. There will be no interim analysis.

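### The only stated power (80%) belongs to a 360-participant, three-centre design; at the 120 actually targeted, power for the same effects is roughly 26% to 36%, and none is stated

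*Protocol article*

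**What the plan says.** The Sample size section first describes a trial of 360, planned for a Cochran-Mantel-Haenszel (CMH) test with three recruitment centres as strata and 1% six-month cessation on placebo. The basis is "A sample size of 180 in the NAC group and 180 in the control group (across three roughly equal size strata"), which "achieves 80% power to detect an odds ratio (OR) = 7, assuming a two-sided type I error of 0.05". The same 360 is also said to give 80% power for a 7-point difference after an 8% inflation for clustering. The section closes with the present target: "However, the current trial has a recruitment target of 120 in total, with the intention of scaling up as more funding is acquired".

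The abstract and the Overview confirm 120 participants, and the Overview names two sites, not three. Allocation is 1:1, so 60 per arm. The article gives no power and no detectable difference for that size.

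The confirmatory framing is unchanged. The first hypothesis is that "treatment with NAC will be superior to placebo for smoking cessation at follow-up (week 42"), and the Statistical analysis section says "All comparisons will be conducted using a two-sided alpha level of 0.05". That section also says "There will be no interim analysis", and Allocation and concealment keeps the randomisation code hidden until data analysis is complete.

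**The concern.** A sample size section exists to tell the reader what the trial can detect. Here it answers that for a design three times larger, with one more centre, and leaves it open for the trial being run. The effects it names, the placebo rate and the alpha are all carried over; only the number of participants changes.

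At stake is how a null result will be read. If the trial has well under an even chance of detecting a 7-point gain, a non-significant result at 120 is the likely outcome even when that gain is real. Without a power figure or detectable effect for 120, nothing in the plan prepares the reader for this. The Conclusion meanwhile looks ahead to rapid adoption in practice if the result is positive.

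A smaller question is what happens to the 120 if more funding arrives. The article does not say whether they would be analysed on their own first, or how they would be combined with later participants.

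**Working it through.** **Inputs** (Sample size section unless noted): placebo rate 1%; odds ratio 7, or a 7-point difference (1% vs 8%); two-sided alpha 0.05 (z = 1.96); 180 per arm in the stated calculation; 8% clustering inflation attached to the 7-point figure; target 120; 1:1 ratio (Allocation and concealment), so 60 per arm; two sites (Overview). The 1% attrition figure is ignored; its effect on power is negligible.

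An odds ratio of 7 on 1% gives p2 = 7 × 0.01 / (1 − 0.01 + 7 × 0.01) = 0.07 / 1.06 = 6.6%.

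**Formula.** Power = Φ[(d − c − 1.96 × SE0) / SE1], where d = p2 − p1, SE0 = √(2p̄(1 − p̄)/n) with p̄ the mean of the two rates, SE1 = √((p1(1 − p1) + p2(1 − p2))/n), and c = 0 without continuity correction or 1/n with it.

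**Step 1: reproduce the stated 80%.**

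- Odds ratio 7, n = 180, no correction: d = 0.0560, SE0 = 0.02016, SE1 = 0.01994. (0.0560 − 1.96 × 0.02016)/0.01994 = 0.83, so power is 79.6%.
- 1% vs 8%, with correction and inflation: effective n = 180/1.08 = 166.7, c = 0.0060, SE0 = 0.02271, SE1 = 0.02238. (0.07 − 0.0060 − 1.96 × 0.02271)/0.02238 = 0.87, so power is 80.8%.

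Both stated figures reproduce, each under its own convention.

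**Step 2: the same two calculations at 60 per arm.**

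- Odds ratio 7, n = 60: SE0 = 0.03492, SE1 = 0.03454. (0.0560 − 1.96 × 0.03492)/0.03454 = −0.36, so power is 36.0%.
- 1% vs 8%, effective n = 60/1.08 = 55.6: c = 0.0180, SE0 = 0.03933, SE1 = 0.03877. (0.07 − 0.0180 − 1.96 × 0.03933)/0.03877 = −0.65, so power is 25.9%.

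The second figure is lower despite the larger effect because only it carries the correction and the inflation.

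**Step 3: sensitivity to the test.** Exact binomial enumeration at 60 per arm, and simulation of the CMH test with two strata of 30 per arm:

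| Effect | Chi-square, uncorrected (exact) | Fisher (exact) | CMH uncorrected | CMH corrected |
|---|---|---|---|---|
| 1% vs 6.6% | 34.7% | 12.6% | 35.1% | 12.7% |
| 1% vs 8% | 47.0% | 22.7% | 47.7% | 22.8% |

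The exact tests span 13% to 47%, and the simulated stratified test agrees to within one percentage point. Applying the 8% inflation to both effects (about 56 per arm) lowers the span to about 10% to 44%.

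**Step 4: detectable effect at 60 per arm, placebo 1%.** The exact uncorrected chi-square test reaches 80.8% power at 13% on NAC. The normal approximation reaches 81.5% at 15%. Fisher's test gives 79.7% at 15.5% and 82.1% at 16%. So 80% power needs about 13% to 16% against 1%, a gain of 12 to 15 points, or roughly twice the 7 points planned for.

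**Step 5: type I error under two readings of the extension.** If enlargement depends on funding alone and no by-arm data are seen, there is one test at 0.05 and the error rate is 5%. If instead the 120 were tested at 0.05, then pooled and retested at 0.05 with 360, the two statistics would have correlation √(120/360) = 0.577. The chance that at least one exceeds 1.96 in absolute value under the null is then 8.8% (bivariate normal).

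**The case against.** The strongest reply is that nothing is hidden or miscalculated. The section says that 360 was the initial figure, ties 80% to 180 per arm, and states the cut to 120 in the same paragraph. That stands: a reader might infer that the protocol claims 80% power for 120, or that its arithmetic is wrong, and the text supports neither. What is missing is the consequence of the cut. This is also not detail that a journal article would leave to a fuller document, because the article prints a complete justification, only for a different design.

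A second reply is that 13% to 47% mixes tests, and that Fisher's test is not planned. That is fair, so the like-for-like figures of 36% and 26% lead here and the wider range is shown as sensitivity.

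Third, the pilot quit rates in the Introduction (47.1% vs 21.4%) would give about 85% power at 60 per arm. They come from a 12-week pilot with 17 participants per arm, at a different dose and alongside cognitive behavioural therapy. The protocol did not plan on them.

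Fourth, the analysis section already commits to the common odds ratio with its 95% confidence interval. That meets part of the need; what remains is to say how a non-significant result is to be read.

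Finally, a reader might infer that the intention to scale up inflates the type I error. The documents do not support that. The stated trigger is funding, not results; no interim analysis is planned; and the code stays concealed until analysis is complete. The 8.8% arises only in a test, pool and retest sequence that the article does not describe.

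**Conclusion.** The point holds as a justification that was not updated, not as an arithmetic error. The trial being run does not have the only power its protocol states. With the methods that reproduce 80% at 360, power at 60 per arm is about 36% for the odds ratio of 7 and about 26% for 1% vs 8%. Every test considered leaves it below 50%. This rests on the protocol's own 1% placebo rate, effect sizes and alpha, and on equal arms of 60.

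On the extension, only a clarification is warranted. Type I error is 5% if enlargement is decided without by-arm data, which is what the concealment and no-interim rules imply but do not spell out for this case.

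**What to change.** In the Sample size section, replace the justification based on 360 with one for 60 per arm at two sites. It should give the power for the two named effects (about 36% and 26% by the methods above, or the figures for whichever version of the CMH test is planned) and the detectable effect (80% power only for about 13% to 16% against 1%, depending on the test). The 360 calculation can stay as background, marked as belonging to the larger design.

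Add one sentence saying that a non-significant result at 120 does not rule out the 7-point effect and will be interpreted through the 95% confidence interval.

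Add one sentence saying that any extension is triggered by funding and decided without by-arm data, in line with the concealment rule and the absence of an interim analysis.

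The cost is wording: the stated power becomes less favourable, and no participants, visits or analyses are added. Neither relabelling the trial as a pilot nor splitting alpha is needed to settle this point.

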#### Statistical analysis

A modified ‘intention-to-treat’ approach, following CONSORT Statement guidelines, will be used. Missing values will be scrutinized to check for non-random distribution and analyses that utilize baseline data will be executed twice: once using observed data and once using multiple imputation under multivariate normal assumptions. The CMH test will be used to compare the proportions of relapse between the treatment groups (control versus intervention). The common OR and its 95% confidence interval will also be reported as well as the results of the Breslow-Day test for homogeneity of the ORs across the strata. In further supportive analyses, generalized linear mixed models (GLMMs) will be used to compare the rates of relapse after adjusting for baseline measurements and to explore possible interactions between baseline factors and the intervention. Average treatment group differences for the continuous secondary outcomes will be examined using a likelihood based mixed-effects model, repeated measures approach (MMRM). The MMRM models include the fixed categorical effects of treatment, visit and treatment-by-visit interaction, as well as the continuous fixed covariates of baseline score and baseline score-by-visit interaction. Effect sizes will be calculated using Cohen’s guidelines. All comparisons will be conducted using a two-sided alpha level of 0.05. There will be no interim analysis.

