### Withdrawal criteria

Participants are withdrawn from the trial under the following conditions: failure to take the trial medication for seven consecutive days; pregnancy; emergence of serious AEs suspected to be associated with the trial medication; or commencement of a different pharmacotherapy for smoking cessation during the 16-week treatment phase. Participants will be questioned about these events and their adherence to the study protocol at the bi-weekly telephone interviews during the treatment phase of the study. Withdrawal of consent at any time in the study will result in immediate withdrawal from the trial.

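### The only stated missing-data methods suit a rare yes/no abstinence outcome poorly and do not count missing as smoking, and follow-up after withdrawal is left open

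*Protocol article*

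**What the plan says.** All references are to the protocol article.

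- **Statistical analysis.** The analysis set is a modified intention-to-treat set, and the modification is not described. Analyses that use baseline data are done "once using observed data and once using multiple imputation under multivariate normal assumptions"; neither run is named as the main one. The CMH test compares relapse proportions, with no baseline covariate named. Mixed models (GLMMs) of relapse adjusted for baseline are supportive, and MMRM is used for continuous secondary outcomes.
- **Withdrawal criteria.** "Participants are withdrawn from the trial under the following conditions: failure to take the trial medication for seven consecutive days". A further condition is "commencement of a different pharmacotherapy for smoking cessation during the 16-week treatment phase". The section does not say whether withdrawn participants are followed to week 42.
- **Variables and instruments.** The primary outcome is continuous abstinence from week 16 to week 42. After Table 1, those who never quit or who relapse are pooled as treatment failures; participants with unknown status are not mentioned. The same text makes bupropion, varenicline or NRT use a withdrawal criterion within the 16-week treatment period. It then says of NRT use at any point in the 42-week study that "it is not a study withdrawal criterion and these participants may remain in the study".
- **Sample size.** Placebo cessation is planned at 1%, with the phrase "including participant attrition estimated at 1" per cent.

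**The concern.** The outcome is binary and planned to be rare, so the result depends on a handful of abstainers and on who is in the denominator. An observed-data run removes everyone without an outcome. A multivariate-normal model treats a 0/1 variable as Gaussian. Its imputed values are not 0 or 1, and the plan does not say how they would enter a relapse model.

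The missingness may also be related to the outcome. Going seven days without medication, or starting another cessation drug, can plausibly follow a failed quit attempt. If such participants leave the trial and are not seen at week 42, those who remain are a favourable selection. Reported quit rates would then be too high, and any difference in loss between arms would pass into the treatment comparison.

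**Working it through.** **1. The plan's own figure.** Inputs from Sample size: "A sample size of 180 in the NAC group and 180 in the control group", which "achieves 80% power to detect an odds ratio (OR) = 7", "assuming a two-sided type I error of 0.05", with 1% on placebo.

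- Odds ratio 7 on 1%: odds 7 × 0.01/0.99 = 0.0707, so the NAC rate is 0.0707/1.0707 = 6.6%.
- n per arm = [1.960·√(2p̄q̄) + 0.842·√(p₀q₀ + p₁q₁)]² / (p₁ − p₀)², with p̄ the mean rate, gives 182. Power at 180 per arm is 0.796.
- 1% vs 8% with continuity correction: 164 per arm; × 1.08 for clustering = 177; / 0.99 = 179.

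The stated 180 per arm reproduces, so this point does not rest on a sample-size error.

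**2. Expected events at the current target.** With 120 participants, 60 per arm: 60 × 0.01 = 0.6 abstainers on placebo and 60 × 0.08 = 4.8 on NAC.

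**3. Observed cases when there is no true effect.** Assumptions, not in the documents: 5 of 60 abstinent in each arm (8.3%), every lost participant smoking, and the loss rates shown.

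- 30% lost in both arms: 5/42 = 11.9% instead of 8.3%.
- 40% lost on NAC, 20% on placebo: 5/36 = 13.9% vs 5/48 = 10.4%; OR = (5/31)/(5/43) = 1.39.
- Reversed: OR = (5/43)/(5/31) = 0.72.
- 1% lost: 5/59.4 = 8.4%.

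**4. Observed cases at the planning rates.** True rates among all randomised are 8% and 1% (7.0 points, OR 8.6), with every missing participant smoking. Observed rate = true rate / (1 − loss).

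| Loss NAC / placebo | Observed rates | Difference (points) | OR |
|---|---|---|---|
| 1% / 1% | 8.1% vs 1.0% | 7.1 | 8.6 |
| 20% / 20% | 10.0% vs 1.2% | 8.7 | 8.8 |
| 40% / 40% | 13.3% vs 1.7% | 11.7 | 9.1 |
| 40% / 20% | 13.3% vs 1.2% | 12.1 | 12.2 |
| 20% / 40% | 10.0% vs 1.7% | 8.3 | 6.6 |

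Equal loss mainly inflates the rates and their difference. Unequal loss moves the odds ratio, in either direction. Under these assumptions, counting missing as smoking returns 8.0% vs 1.0% at any loss rate.

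**5. Normal model for a rare binary variable.** With mean p, SD = √(p(1 − p)) and P(draw < 0) = Φ(−p/SD).

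- p = 5%: SD 0.218, 41% of draws below 0.
- p = 8%: 38%.
- p = 1%: 46%.

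If draws were rounded at 0.5, a 5% rate would become about 2%. The plan does not mention rounding, so this last figure is only illustrative.

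**6. Withdrawal text side by side.** For NRT in the first 16 weeks, Withdrawal criteria and one sentence after Table 1 lead to withdrawal; the sentences that follow say the participant may stay. The passages decide who is withdrawn and must be reconciled.

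**The case against.** The strongest objection is scope. The two-run rule is limited to analyses that use baseline data, and the CMH test names no baseline covariate, so the rule need not reach the main comparison. This stands. It is wrong to say that the plan fixes observed-case and normal-imputation analysis for the primary test. It does not clear the plan, because the baseline-adjusted relapse models are within the rule and the CMH test is left with none.

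Second, a journal article may leave the definition of the modified set and the sensitivity analyses to an analysis plan. That is fair, and silence on those details alone would not be a finding. What the article does state is an imputation model poorly suited to its binary outcome, and withdrawal from the trial rather than from treatment.

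Third, participants recorded as never having quit or as relapsed, through the fortnightly calls or the visits, could already be classed as treatment failures. This reduces the problem, but those lost with unknown status remain uncovered.

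A reader might infer more: that withdrawn participants are excluded from the analysis, that imputation gives dropouts completers' quit rates, and that cessation is necessarily overstated in both arms. The documents do not support this. They do not say that withdrawal ends follow-up or removes anyone from the analysis set. Imputation conditions on its covariates, which could include week-8 and week-16 CO and cotinine, and matches completers' rates only if those are uninformative or omitted. Draws below zero do not by themselves bias an unrounded mean. Overstatement depends on dropouts being smokers.

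**Conclusion.** The point holds in this form: the article leaves the modified intention-to-treat set undefined, its only stated missing-data methods suit a rare binary outcome poorly and do not count missing or unconfirmed abstinence as smoking, and it does not secure week-42 outcomes after withdrawal.

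The size depends on loss rates that the documents do not give. If lost participants are smokers, 20% to 40% equal loss shows a difference of 8.7 to 11.7 points instead of 7.0, and unequal loss moves the planning odds ratio of 8.6 to between 6.6 and 12.2. The direction of bias in the treatment effect is therefore unknown.

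If the Sample size phrase means 1% attrition and that is achieved, the bias is negligible (7.1 against 7.0 points). The phrase can also be read as a 1% cessation rate that already treats attrition as failure. On that reading, an observed-case analysis would conflict with the planning assumption.

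**What to change.** 1. Make the primary CMH analysis include all randomised participants, with missing or unconfirmed abstinence from week 16 to week 42 counted as not abstinent. Delete the word modified, or define it consistently with this.
2. State that outcome collection to week 42 continues after study medication stops, unless consent is withdrawn.
3. For the binary outcome, replace multivariate-normal imputation with logistic chained-equation imputation as a sensitivity analysis. With about five expected abstainers, its model must be kept small.
4. Add a delta-adjusted or tipping-point analysis by arm. It is needed because counting missing as smoking is itself an assumption and can mislead if lost participants include abstainers and loss differs by arm.
5. Keep MMRM for the continuous scales.
6. Reconcile Withdrawal criteria with the text after Table 1 on NRT use during the treatment phase.

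The cost is analysis-plan wording, some extra contact attempts using the existing week-42 visit, and slightly lower reported quit rates. The article describes recruitment as ongoing, plans no interim analysis and keeps the code concealed until analysis is complete, so the change can be made before unblinding.
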